### Declarations

This study will be conducted following the principles in the Declaration of Helsinki and approved by the Human Research Ethics Committee at the Federal University of São Carlos (Date: February 2018, Study ID#791060170.0000.5504, UFSCar, Brazil). This study is registered in the Brazilian Clinical Trial Registry (RBR-83pwm3). The authors followed the SPIRIT (Standard Protocol Items: Recommendations for Interventional Trials) guidelines for writing clinical trial protocols [30].

During the consent process, the researcher will clarify the objectives and procedures to be used in the research, including details of the methods to be used, the risks and benefits, and stating the possibility of inclusion in either group. The consent also provides a full guarantee of the freedom of the participant to refuse to participate or withdraw their consent at any stage of the research, without any penalty, and shall maintain the confidentiality and privacy of the participants during all phases of the study. All participants will be asked to provide written informed consent prior to enrollment in the study. In the case an individual is unable to sign, an imprint of the thumb will be requested as evidence of consent. All participants will receive a copy of the consent form approved by the ethics committee.

Data and materials from this clinical trial will be made publicly available at the Federal University of São Carlos (UFSCar). The funding sources for this study are FAPESP (Fundação de Amparo à Pesquisa do Estado de São Paulo; grants: 2017/25185–4 and 2017/13655–6). The authors declare they have no competing interests. The author contributions to this protocol and manuscript are as follows: Study design: [name], [name], [name], AB, [name], [name], and [name]. Drafting the manuscript: [name] and [name] Reviewing and editing the manuscript: [name], [name], [name], AB, [name], [name], and [name].

### Study setting and recruitment

Potential participants will be identified from the health information contained in the medical reports of the School Health Unit and Basic Health Units of the University Hospital, Santa Casa in São Carlos and from the local community using advertisements such as posters and pamphlets.

Potential participants will be screened to determine if they meet eligibility criteria (Table 1), participate in the process of informed consent, and then an initial assessment will be conducted to collect data regarding the sample characterization. The screening, consent and initial assessment will perform in a single day at the individual’s home to ease the burden on participants for transportation. This screening will include a brief medical history and physical examination to verify the eligibility criteria of the individuals. Subsequently, eligible individuals will undergo evaluation of the sensorimotor and cardiopulmonary measures.

Participants will be evaluated on study outcome measures at four time points: baseline, 3 days, 30 days, and 90 days after completion of the protocol. All evaluations will be conducted across two days, with a minimum interval of 24 h and a maximum of 3 days between evaluation days.

Participant screening will include medical history, Mini-Mental Status Examination, physical examination (anthropometric data), active and passive range of motion assessment using goniometer and the questionnaire of the use of the affected upper extremity *Motor Activity Log* (MAL). Moreover, muscle tone assessment by Modified Ashworth Scale [31, 32], upper extremity sensorimotor impairment assessment using Fugl-Meyer Assessment (UE-FMA) [33], Manual preference will be assessed by the Edinburgh Handedness Inventory [34], considering hand preference before the stroke. After screening, if the individuals meet the inclusion criteria, then they will be asked to complete a clinical exercise test conducted by a cardiologist.

The sensorimotor and cardiopulmonary function evaluation will take place in the Physical Therapy Department at UFSCar over two days. On the first day, the assessment of using the affected upper extremity by *Motor Activity Log* (MAL) [35–37], sensory deficit of the upper limb by the Nottingham Assessment Sensory (NAS) [38, 39] and motor function by the *Wolf Motor Function Test* (WMFT) [40, 41] will be carried out, followed by the cardiopulmonary exercise test [42, 43] to determine the training parameters of the AE. On the second day, manual dexterity will be assessed by the *Box and Block Test* (BBT) [44] and the *Nine-Hole Peg Test* (NHPT) [45, 46]. The three-dimensional kinematic analysis will be followed by kinematic analysis of sensorimotor functional activity and the quality of life questionnaire (SS-QOL) [47].

### Primary outcome measures

#### Self-reported upper limb use

Motor Activity Log (MAL) [35–37] is a structured interview that evaluates the spontaneous use of the more affected upper limb. Each item independently asks about how much and how well the most affected upper limb is used in daily activities over the last week. A 6-point amount of use scale (score range, 0–5) quantifies how much the affected arms are used and a 6-point quality of movement scale (score range, 0–5) quantifies how well the affected arms are used [48]. Scores on this measure have adequate reliability and validity in individuals with stroke [35, 36].

#### Manual dexterity

The Box and Block Test (BBT) [44] is a measure of gross manual dexterity consisting of a box divided by a partition into two equal-sized compartments and 100 2.5 cm square wooden blocks. The box will place on the side containing the blocks toward the tested hand. The task is to move the maximum number of wooden blocks, one at a time, across the partition in the middle of the box within 60 s. The hand must crossover the barrier to score one block. Multiple blocks carried over at the same time count as a single block. One practice trial will be performed before the assessment. The score recorded is the number of blocks that were moved for 60 s [44]; the average of three tests will be used to calculate the BBT score. The evaluation will be filmed with a camera placed at a standard position and distance; scoring will be confirmed by evaluation of the video recording.

The Nine-Hole Peg Test (NHPT) [45] assesses fine manual dexterity. The test consists of a nine-peg wooden board with nine holes and a container with nine pegs. The side with the pegs will be placed toward the affected upper limb, and the pegs are picked up and placed in the holes, one at a time, and then removed and placed back in the container [45]. If a peg is dropped, then the examiner quickly places it (or a replacement) in the container. One practice trial will be given before the assessment. The score is recorded as the time in seconds necessary to perform the test [46], and the total score will be calculated by the average of the three trials. The time taken to complete the examination will be recorded with a maximum time of 180 s [46]. If the person does not have enough skill to complete the test, then the pegs/s will be calculated using the number of pegs placed [49] compared to the time limit of 180 s. The evaluation will be filmed with a camera placed at a standard position and distance; scoring will be confirmed by evaluation of the video recording.

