## Methods

This study is a randomized, single-blinded, intention-to-treat controlled clinical trial in which 78 participants of both genders in a chronic stage poststroke will be randomized into two groups of 39 participants. One group will receive AE combined with m-CIMT, and the other group will perform stretching exercises combined with m-CIMT. The eligibility criteria are presented in Table 1.

**Table 1 Tab1:** Eligibility criteria

Inclusion criteria	
• Stroke resulting in hemiparesis at least six months prior (chronic) • Do not a present lesion in the two hemispheres • Clinical diagnosis of ischemic or hemorrhagic stroke • ≥ 35 and ≤ 80 years old • Participants must present a minimum active movement of 45° of shoulder flexion or abduction, 20° of elbow extension, 10° of wrist extension, 10° of abduction or extension of the thumb, and 10° extension in at least two fingers (metacarpophalangeal and interphalangeal joints) and thumb • Participants must present the ability to pick up a towel using any grip [28] • Participants must present asymmetric of upper extremity, ≤ 2.5 in the Motor Activity Log (MAL) Quantity Scale [10] • Participants must have the ability to remain seated without trunk and arm support for 1 min [29]	
Exclusion criteria	
• Upper limb movement deficits attributable to no stroke pathology	
• Clear signs of dementia or cognitive disorder, indicated in the Mini- Mental State Examination (scores based in years of education, below 13 for illiterate individuals, 18 for individuals with 1 to 7 years of the primary school and 26 for individuals over eight years after primary school) [30, 31] • Individuals with lesion in cerebellar	
• The individuals are smokers, alcohol, or users of illicit drugs at the time of evaluation • Individuals with structural alterations in the cardiovascular and respiratory systems that will contraindicate the aerobic exercise • Individuals with uncorrected auditory and visual deficits • Individuals who present any electrocardiogram alteration or not the cardiorespiratory stress test • Individuals with historical diseases or osteomioarticular alterations • Individuals with body mass index > 28 • Individuals with uncontrolled diabetes mellitus or hypertension, comprehension aphasia, apraxia	

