### Sample size

The sample size was calculated with G*Power software using the independent t-test, 85% power, alpha 0.05, and 20% drop-out. Data from the Nine-Hole Peg test proposed by Yoon et al. (2014) [29] were considered for this calculation. Thus, a sample size of 78 individuals (39 per group) is required for this study (Fig. 1). However, after collecting the first five participants per group, the sample size will be recalculated for the same variable.

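### The Nine-Hole Peg Test is given in seconds for those who finish and in pegs per second for those who do not, with no rule to bring the two onto one scale

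*Protocol article*

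**What the plan says.** All references are to the protocol article.

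- **Manual dexterity (under Primary outcome measures).** The apparatus has nine pegs: "The test consists of a nine-peg wooden board with nine holes and a container with nine pegs". The score is a time: "The score is recorded as the time in seconds necessary to perform the test". Trials are combined by a mean: "the total score will be calculated by the average of the three trials". There is a ceiling: "The time taken to complete the examination will be recorded with a maximum time of 180 s". For those who fail to finish: "If the person does not have enough skill to complete the test, then the pegs/s will be calculated using the number of pegs placed", set against the 180 s limit.
- **Sample size.** The calculation names one variable: "Data from the Nine-Hole Peg test proposed by" an earlier cited study. The planned recalculation after five participants per group uses that variable again.
- **Statistical analysis.** Every dependent variable goes through the same scheme: two-way repeated-measures ANOVA, or Friedman, Wilcoxon and Mann-Whitney tests if the distributional checks fail.
- **Table 1 (eligibility).** Minimum active movement is required at shoulder, elbow, wrist, thumb and fingers. The grasp criterion is "Participants must present the ability to pick up a towel using any grip". No criterion refers to finishing the NHPT.

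**The concern.** Seconds and pegs per second run in opposite directions and differ by orders of magnitude. The article does not convert completers to a rate, does not say that a non-completer contributes 180 s, and does not describe separate analyses. It also gives no rule for a participant who finishes some of the three trials but not others.

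If both quantities go into one NHPT variable, the weakest hands receive values close to zero, which on a time scale is the best possible result. A treatment that turns non-completers into completers would then be penalised for doing so. The ordering itself is wrong, so the non-parametric fallback inherits the fault.

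The NHPT is the fine-dexterity measure among the primary outcomes and the only variable named in the sample-size calculation. The recalculation rests on ten participants, so a single near-zero entry could distort its mean and standard deviation.

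**Working it through.** **The plan's own figure.** The 78 (39 per group) cannot be fully reproduced, because the article gives no NHPT difference, standard deviation or effect size. The drop-out step is consistent with 31 evaluable per group: 31 / (1 − 0.20) = 38.75, rounded up to 39, and 2 × 39 = 78. Solving an independent t-test for 31 per group, 85% power and alpha 0.05 gives an implied standardised effect of 0.774 two-sided or 0.689 one-sided. The article does not state sidedness.

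**Range of each score.** Inputs are nine pegs and 180 s, both from Manual dexterity.

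- Non-completer: pegs placed / 180. No pegs gives 0, four give 4/180 = 0.022, eight give 8/180 = 0.044. Someone who places all nine but runs out of time removing them gets 9/180 = 0.050.
- Completer: time in seconds, up to 180.

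Read as a time, 0 to 0.050 lies below any achievable completion time. Every non-completer therefore ranks ahead of every completer, and placing no pegs earns the best possible score.

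**One participant who improves.** Eight pegs in 180 s at baseline, then finishing in 170 s: as written, 0.044 becomes 170, an apparent large worsening. On pegs per second for all, 0.044 becomes 9/170 = 0.053, an improvement. On capped seconds, 180 becomes 170, also an improvement.

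**Averaging three trials.** Suppose two trials finish in 170 s and the third ends with eight pegs placed. If the rate is substituted for that trial, the mean is (170 + 170 + 0.044) / 3 = 113.3. With 180 s it is (170 + 170 + 180) / 3 = 173.3. Failing a trial would give a better score than finishing all three in 170 s. Trial-by-trial substitution is an inference; the article does not state it.

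**Illustrative loss of power.** Assumptions, none taken from the article: 31 per group, log-normal latent time with log SD 0.6, true benefit of 0.775 SD on the log scale (0.77 in the t-test runs), two-sided alpha 0.05, one post-treatment comparison. Power means a significant result in the correct direction.

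| Controls unable to finish | Mann-Whitney, as written | t-test, as written | Wrong sign of mean difference, as written (t-test runs) |
|---|---|---|---|
| 5% | about 63% | 60% | 1% |
| 10% | about 40% | 39% | 5% |
| 20% | about 13% | 10% | 24% |
| 30% | about 3% | 2% | 52% |

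On a common scale, Mann-Whitney power is about 83% throughout, whether pegs per second or capped seconds is used. The t-test gives about 77–79% on pegs per second and about 80–84% on capped seconds.

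**The case against.** The strongest reply is that the article never says the two quantities share one column. The sentence just before the pegs-per-second rule caps the recorded time at 180 s. A non-completer could therefore contribute 180 s, correctly ranked last, with pegs per second as an additional description. On that reading nothing is reversed. The rule also cites sources that are not at hand, and a condensed article may leave such handling to a fuller document.

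This has force. A reader might infer that the inversion is certain; the documents do not support that. It follows from the most literal reading and is not stated. But the capped reading is not stated either, and this is more than an omitted detail: the article fixes a scoring rule with two units and leaves them unreconciled. Analysing the units separately would not rescue it. Non-completers would leave the time analysis because of their outcome, and participants could change variable between visits, in a trial described as intention-to-treat.

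Four further objections stand:

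- The non-completer rule is worded for the person, not the trial, so mixing units within one participant's average is only possible.
- Table 1 asks for more than grasping a towel. Non-completers are foreseeable, since the article provides for them, but their frequency is unknown.
- A reader might take the simulated figures as this trial's power. They are not. The plan sets p < 0.012 for Mann-Whitney and p = 0.005 for the planned ANOVA comparisons, across four visits.
- The Motor Activity Log and the Box and Block Test, also primary, are unaffected.

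**Conclusion.** The point holds as a badly fixed scoring rule. The NHPT carries two units with opposite directions, with no rule to combine them and none for partly completed trial sets. That the as-written scores put non-completers first follows from nine pegs and 180 s alone. Whether the analyst would actually enter them that way is not settled by the text.

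The size of the damage depends on the non-completion rate. With few non-completers the loss is moderate; under the stated assumptions, at 30% of controls the as-written analysis has almost no power and the estimate is about as likely to point the wrong way as the right way. The assumed effect is close to what 31 per group implies for a two-sided test. The log SD and the non-completion rates have no source in the article.

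The rule should be settled before the recalculation at five per group and before any comparison of the groups.

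**What to change.** State one monotone NHPT scale for every participant, trial and visit. Either choice works:

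- **Pegs per second for all:** 9/time for completers, pegs placed/180 for non-completers. Someone with all nine placed but not all removed ties at 0.050 with a completer at exactly 180 s, so the order is never reversed.
- **Seconds for all:** non-completers are set to 180 s, the worst rank.

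Average the three trials on the chosen scale, including sets in which only some trials are finished. Report the other scale as a sensitivity analysis. Use the chosen scale in the sample-size recalculation, re-expressing the assumed effect if that scale is pegs per second.

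The cost is one or two sentences. Time, pegs placed and video are already recorded. Pegs per second is less familiar to clinicians and sets placing plus removing (completers) beside placing only (non-completers). Capped seconds keeps the stated unit and needs no new effect assumption, but ties all non-completers and so hides change among them.

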### Secondary outcome measures

#### Sensorimotor function

The Nottingham sensory assessment (NSA) [38, 39] will be used to evaluate the sensory deficits (protopathic and epicritic sensory modalities). This assessment has excellent intra- and interrater concordance coefficients and high internal consistency and concurrent validity. There are four subscales: (1) tactile sensation, (2) proprioception, (3) stereognosis, and (4) discrimination between two points on the face, trunk, shoulder, elbow, wrist, hand, knee, ankle, and feet. The tactile sensation subscale evaluates light touch, pressure, pain, tactile location in both limbs and simultaneous bilateral contact. Given that the score on each item ranges from 0 to 2, the total score for the less-affected side ranges from 0 to 90 and the most affected from 0 to 108.

The proprioception subscale evaluates the execution of a movement, its direction, and the articular position of the segments of the more affected half-body. This score varies from 0 to 3, with a total score of 21. The face, trunk, and feet are not evaluated. Stereognosis evaluates the recognition, using the more affected hand, of the following objects: ten centavos, 25 centavos, and one real coin, a pencil, a pen, a comb, scissors, a sponge, a cloth, a glass, and a teacup. The score varies from 0 to 3, with a total score of 21.

The discrimination between points will be tested on the index finger and thenar region; the score varies from 0 to 2, having a total score of 4.

#### Motor function

The Wolf Motor Function Test (WMFT) [40, 41] assesses upper limb functional ability in 17 tasks, measuring the speed of task execution in seconds, the quality of movement through the functional ability scale (FAS), and the strength of grip and shoulder flexion in specific tasks. The execution time total will be quantified by the mean and the median of the FAS scores. The evaluation will be filmed with a camera placed at standard position and distance, and the time and quality of performance will be assigned through analysis of the video.

### Cardiopulmonary testing

Cardiopulmonary exercise testing [42, 43] will be used to determine the training parameters of the AE. Specifically, this test will be used to evaluate the aerobic power and determine the ventilatory anaerobic threshold. The analysis will be performed on an ergometric bicycle (CORIVAL V3, Lode BV, Groningen, Holland). For the test, initially, the participant will stay on the bike resting for one minute. Then, the exercises will start and will be without loads for three minutes; after this, the load increment will start. Power will be calculated for each participant according to the formula described by Wasserman [50]. The increase varies from 10 to 20 watts. Individuals will be instructed to maintain a cadence of 50–60 rpm throughout the test. The test duration will be between 8 and 12 min. The interruption criteria will be as follows: decrease or abnormal heart rate and blood pressure during exercise, presence of arrhythmias, ischemic changes on the electrocardiogram, respiratory distress, dyspnea [42], subjective perception of effort classified as intense [51] or a decrease in cadence below 50 rpm. The metabolic and ventilatory variables, such as pulmonary ventilation (liters\min-1), oxygen consumption and carbon dioxide production (liters\min-1), ratio respiratory exchange, efficiency for oxygen consumption, carbon dioxide and heart rate will be analyzed and captured using an expired gas measurement system (ULTIMA medGraphics-Breeze, St. Paul, Minnesota, USA) and with Breeze Suite 7.1 software (MedGraphics, St. Paul, Minnesota, USA).

### Upper limb performance in 3D kinematics

Three-dimensional Motion Analysis (3DMA) of three functional activities will be quantified using the optoelectronic ProReflex Motion Capture System (Qualisys Medical AB, Gothenburg, Sweden) with eight high-speed cameras at a sampling frequency of 120 Hz. One trained physiotherapist will perform this analysis following the standard protocol of the International Society of Biomechanics (ISB) [52]; (1) placement of clusters on trunk, hemiparetic scapula, arm, forearm, and hand [52–55], (Fig. 2); (2) collection of seated static posture for five seconds; (3) ten passive circumduction movements of the shoulder (right and left sides) to calculate the glenohumeral joint center [56]; (4) removal of anatomical markers; and (5) collection of 3D kinematics during the functional tasks.

**Fig. 2 Fig2:**
[figure not shown]
Marker placement for 3D kinematics of the upper limb: A total of 16 markers will be used. Participants will be seated in a chair without back support at an adjustable table at the height of the xiphoid process. **a** Side view: Markers are located on the acromioclavicular joint, lateral and medial epicondyle, midline of the forearm in the direction of the ulnar and radial styloid process. Marker clusters will be placed on the scapula and on the in insertion of the deltoid muscle, 5 cm below the cubital fossa. **b** Front view: Markers will be located on the most ventral point of the sternoclavicular joint, xiphoid process, jugular notch, the base of the proximal phalanx of fingers 2,3 and 5, and the base of the metacarpal of the 3 fingers. Marker clusters will be located on the base of the 3rd metacarpal, the metacarpophalangeal joint of the thumb, digits 2 and 5 and, the tips of the thumb and forefinger and the carpometacarpal joint. **c** Rear view: spinous process C7 and T8, scapula root, lower angle of the scapula. Marker clusters will be located on the thorax between C7 and T8

Three functional activities will be evaluated: drinking, brushing the hair, and putting a coin inside a pot (Fig. 3). All objects will be placed on a table in the midline at the height of the xiphoid process and a distance of 80% of the upper limb length, except the pot of the third task, which will place on the same side of the paretic limb at 110% of the upper limb length. The first two tasks will be divided into three phases: (1) reaching for the object, (2) transporting to the body (mouth or head), and (3) returning to the table [57, 58]. The third activity will be divided into two phases: (1) reaching for the coin and (2) transporting to the pot and releasing the coin. All tasks will be performed at a self-selected speed four times with the paretic limb. However, the first trial will be used for familiarization. Thirty-second rest intervals between the trials will be provided.

